1. STUDY ENROLLMENT AND WITHDRAWAL

Adult (≥ 18yrs) patients admitted to the Amrita Institute of Medical Sciences and Research Center and meeting all the inclusion and exclusion screening criteria of the study will be enrolled once signed informed consent is obtained. A total of 100 cases of dengue with a thrombocytopenia (peripheral platelet count of ≤30,000/µL) will be enrolled into the two arms of the study. The point of enrollment is defined as the time at which a patient has signed and dated the consent form.

**5.1 Subject Inclusion Criteria**

In order to be eligible to participate in this study, an individual must meet all of the following criteria:

1. Provide signed and dated informed consent form
2. Willing to comply with all study procedures and be available for the duration of the study
3. Male or female, aged ≥ 18 yrs of age. Clinically diagnosed of dengue and a peripheral platelet count of ≤30,000/µL.
4. A laboratory positive diagnosis of dengue confirmed by a positive NS1 or IgM or IgG ELISA test and/or detection of viral RNA by real time PCR assay.

**5.2** **Subject Exclusion Criteria**

Patients with one or more of the following criteria at enrolment will be excluded from the study:

- 1. Pregnancy and lactation.
  2. Patients who has been given steroids for thrombocytopenia and also those who have been transfused platelets before starting the drug
  3. Taking indigenous medicines.
  4. Alanine aminotransferase (ALT) >150 U/L

**5.3 Strategies for Recruitment and Retention**

All patients recruited will be in-patients and we therefore do not anticipate any withdrawals.

**5.4 Treatment Assignment Procedures**

- 1. 1. Randomization Procedures (if applicable)

We will randomly assign enrolled patients in a 1:1 ratio to receive CPLE (Caripill) (1100mg) or placebo once daily for 5 days. Block randomization of will be stratified by age and gender into block sizes of 4 or 6.

**5.4.2 Masking Procedures (if applicable)**

MicroLabs Ltd. will provided CPLE (Caripill) tabs and visually matched placebo without charge. Only the clinical trials pharmacist had access to the randomization list. All other study staff will be blinded to treatment allocation until after completion of the study and database locking.

**5.5 Subject Withdrawal**

Subjects may withdraw voluntarily from the study or the investigator may terminate a subject's participation if:-

- Any clinical adverse event (AE), laboratory abnormality, or other medical condition or situation occurs such that continued participation in the study would not be in the best interest of the subject.
- The subject meets an exclusion criterion (either newly developed or not previously recognized) that precludes further study participation.
  1. Premature Termination or Suspension of Study

This study may be suspended or prematurely terminated if there is sufficient reasonable cause. Written notification, documenting the reason for study suspension or termination, will be provided by the P.I.s If the study is prematurely terminated or suspended, the principal investigator will promptly inform the IRB and will provide the reason(s) for the termination or suspension.

Circumstances that may warrant termination include, but are not limited to:

- Determination of unexpected, significant, or unacceptable risk to subjects.
- Insufficient adherence to protocol requirements.
- Data that is not sufficiently complete and/or evaluable.
- Determination of futility.

1. STUDY INTERVENTION
   1. Study Product Description

Package Insert information on CPLE (Caripill) tabs

- - 1. Acquisition

CPLE (Caripill) and placebo tablets will be supplied by MicroLabs Ltd.

- - 1. Formulation, Packaging, and Labeling

Packaging and labeling of CPLE (Caripill)

- - 1. Product Storage and Stability

The CPLE (Caripill) tabs will be stored at room temperature, away from heat and direct light.

- 1. Dosage, Preparation and Administration of Study Product

CPLE (Caripill) and placebo tabs of 1100mg in strength will be administered orally three times a day for 5 days.

- 1. Assessment of Subject Compliance with Study Product Administration

Each study subject will be directly observed for patient compliance by pill counts by the study nurse co-ordinator.

- 1. Concomitant Medications/Treatments

The treatment plans including the details of the concomitant medications will be recorded in the case record form (CRFs – Appendix I).

1. STUDY SCHEDULE

Screening

All adult patients admitted to Gen Medicine with a history of fever (<72 hr) will be clinically and laboratory evaluated for dengue illness. Subsequent to obtaining and documenting an informed consent form, the study subject will be further screened for detailed laboratory diagnosis for dengue and reviewed clinically for satisfying all study inclusion and exclusion criteria. Details in Schedule of Events

Detailed history and clinical examination will be performed and data recorded in the study CRF. Baseline hematological and biochemical, virological parameters (as part of standard of care) will be sought and recorded in the CRF. Study subject will be administered the study medications on day 1 after confirmed diagnosis as per schedule. Clinical evaluations, laboratory investigations including viral load will be performed during hospital stay.

1. STUDY PROCEDURES /EVALUATIONS

**8.1 Clinical evaluation**

Patients will be followed by a study physician daily until discharge, and all signs and symptoms recorded in the case report form. Clinical management decisions will remain in the hands of the attending doctors, a structured treatment plan will be provided so as to document the dengue management details. In the event that shock or any other serious complication develops, the patient will be transferred to the appropriate ICU. Details of all adverse events will be recorded on specific forms, together with an assessment as to whether the event is likely to be related to any treatment received, and all serious events will be reported promptly to the IRB. Patients who are fit to be discharged on or after study day 5. All patients will be asked to attend a follow-up visit at week 2 and repeat and report the LFT (Liver function test) results via phone.

- 1. Laboratory Procedures/Evaluations
     1. Clinical Laboratory Evaluations

Hematocrit, platelet and CBC measurements will be carried out daily or more frequently if clinically indicated. These tests will be repeated at the follow-up visit. Renal and liver function tests, electrolytes and coagulation profiles, will be carried out at enrolment, 48 hours later, day 5 of illness and at the follow-up visit. If the ALT measured 48 hours after enrolment is greater than 250 U/l, the study drug will be discontinued. It should, however, be noted that hepatic dysfunction might be secondary to dengue infection and could be positively affected by CPLE (Caripill) therapy. Conventional serological and virological tests will be used to confirm dengue infection and identify the infecting serotype. For a small subset of patients (n=20) plasma samples collected at daily intervals until discharge (and daily until day 5 if discharged before day 5) will be assessed for NS1 antigenemia, and concentrations of various pro- and anti-inflammatory cytokines (TNF-α, IFN-γ, IL-6, IL-4).

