**Randomization**

**Treatment Group (N=50)**

**Control Group (N=50)**

**Day 0**

Clinical examination and detailed biochemical, hematological and virological laboratory investigations will be performed at baseline. Peripheral blood (5ml) will be collected; CRF will be completed for each enrolled subject. Administer CPLE (Caripill) or placebo *t.i.d* for 5 days.

Repeat study intervention (*if applicable*).

Follow-up assessments of study endpoints and safety. Appropriate recommended “standard of care” treatment modalities will be employed for each study subject. Routine hematological and biochemical laboratory assays will be done. Administer CPLE (Caripill) or placebo *t.i.d* for 4 more days.

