**Day 4**

Final assessments of study endpoints and safety. Appropriate recommended ‘standard of care” treatment modalities will be employed for each study subject. Routine hematological and biochemical laboratory assays will be done. Administration of final dose of CPLE (Caripill) or placebo *t.i.d* continue

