**Day 5**

Follow up assessments will occur at 2 week interval after the final dose of CPLE (Caripill) or placebo tab including the routine clinical, biochemical, hematological assays.

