**Dengue and Thrombocytopenia**

Thrombocytopenia, marked by a platelet count less than 150,000/µl of blood, is one of the hallmark indicators of severity in dengue viral infections. Typically platelet counts decline steeply during the infection within the initial 4-6 days of onset of fever and revert back to normal levels in the consequent days as the fever subsides. During the phase of defervescence, plasma leakage due to increased vascular permeability could potentially exacerbate the condition, leading to life threatening dengue shock syndrome (DSS) in patients with hemorrhagic fever (DHF) ^6^. Previous studies have reported an association between depleted platelet levels and higher prevalence of clinical bleeding in patients with dengue viral infections^7^. Inadequate platelet levels that fail to suppress bleeding and initiate coagulation could also lead to the bleeding symptoms. One of the several mechanisms proposed to explain thrombocytopenia during the infection of DENV serotypes involves the inhibition of bone marrow progenitor cell proliferation and functions^8^. Decline of megakaryocyte progenitors in the bone marrow has been demonstrated during dengue viral infection in humanized mice, possibly indicating the suppression of platelet production leading to dengue induced thrombocytopenia^9^. Depletion of platelets during dengue viral infection can also be attributed to the activated immune response that destroys platelets by augmented apoptosis, lysis and antibodies^10^. The non-structural protein NS1 is expressed in infected cells, eliciting immune responses. DENV infections also lead to up-regulation of membrane bound Tissue Factor (TF) and activation of platelets. Coagulation and inflammatory pathways are initiated, leading to the release of pro-inflammatory cytokines like TNF-α and IL-6. Raised levels of TNF-α has been associated with hemorrhagic symptoms. Moreover, immune dysregulation can also lead to alterations in platelets functions. Plasma leakage from capillaries has also been associated to altered platelet functions^11^ Endothelial sequestration is another mechanism that leads to thrombocytopenia. Platelets increasingly attach to von-Willebrand factor (vWF) on vascular endothelial cells, resulting in small clogs in microcirculation and low levels of platelets in the peripheral blood^12^.

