- As mentioned in the product monograph, CPLE is contraindicated in males with prostate dysfunction (ie, BPH or prostate cancer); C. papaya should be avoided as it increases the iron absorption. Excess iron may increase oxidative stress, especially in the aging male. Iron overload may increase the risk of developing prostate cancer. Caripill should be used with caution in individuals with bleeding disorders or those taking blood thinning medications such as aspirin or warfarin. In view of this, to ensure patient safety, we will be excluding these patients.
- Patients will be monitored for any liver impairment. Routine biochemical, LFTs (Liver function tests) including serum albumin levels will be monitored on a daily basis. These parameters will be monitored throughout the study period i.e including the hospital stay and follow-up visits.

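### Liver tests are daily in section 2.3.1 but at four time points in 8.2.1, one of them on the illness clock; followed as worded, 8.2.1 can leave the last 2 (or 3) dosing days untested, and the mandatory ALT stop covers only the 48-hour value

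*Protocol*

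**What the plan says.** The risk section, 2.3.1, states: "Routine biochemical, LFTs (Liver function tests) including serum albumin levels will be monitored on a daily basis". It extends this over the whole study period, including the hospital stay and follow-up visits.

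The laboratory section, 8.2.1, makes only haematocrit, platelets and blood count daily. Renal and liver tests, electrolytes and coagulation "will be carried out at enrolment, 48 hours later, day 5 of illness and at the follow-up visit".

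The stopping rule in 8.2.1 reads: "If the ALT measured 48 hours after enrolment is greater than 250 U/l, the study drug will be discontinued". Section 5.5 lets the investigator end a subject's participation for a laboratory abnormality or a newly met exclusion criterion, but this is a permission and not a requirement. ALT above 150 U/L is one of the exclusion criteria (5.2).

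Dosing runs on study days. The Schematic of Study Design starts it at Day 0 ("Administer CPLE (Caripill) or placebo *t.i.d* for 5 days"), and its final-dose box reads "Routine hematological and biochemical laboratory assays will be done. Administration of final dose of CPLE (Caripill) or placebo". Follow-up is then described as: "Follow up assessments will occur at 2 week interval after the final dose of CPLE (Caripill) or placebo tab". Section 8.1 asks patients both to attend at week 2 and to "repeat and report the LFT (Liver function test) results via phone".

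**The concern.** Two sections give different LFT frequencies for the same patients. Section 8.2.1 sets daily blood counts and less frequent LFTs next to each other, so its list cannot be read as shorthand for daily LFTs.

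The list also mixes two clocks. The enrolment and 48-hour samples move with study day, but the third is fixed to the fifth day of illness. The later a patient enters in the illness, the earlier that sample falls within the dosing course, until it adds nothing after 48 hours.

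At stake is whether a late ALT rise is seen while the drug can still be stopped. Staff who follow 8.2.1 may have no result to act on. Staff who follow 2.3.1 will have one, but after 48 hours no mandatory rule applies to it. An ALT of 260 U/L at 48 hours requires discontinuation; the same value at 72 hours does not.

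**Working it through.** The protocol states no figure to reproduce here. The check is a calendar count.

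**Inputs**
- LFTs under 8.2.1: enrolment, 48 hours later, illness day 5, follow-up.
- Dosing: 5 days. The Schematic, read as printed, gives study days 0 to 4. Section 7 refers to giving study medication on day 1 after confirmed diagnosis, so study days 1 to 5 is taken as the alternative.
- Follow-up: 2 weeks after the final dose.
- Illness day at entry: k, with enrolment as study day 0. The eligibility criteria do not fix k.

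**Formulas**
- Illness day 5 falls on study day 5 − k.
- The last scheduled LFT before follow-up is on study day L = max(2, 5 − k).
- Dosing days after it number 4 − L (dosing on days 0 to 4) or 5 − L (dosing on days 1 to 5).

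| Illness day at entry (k) | Study day of illness day 5 | L | Dosing days after L, dosing 0–4 | Dosing days after L, dosing 1–5 |
|---|---|---|---|---|
| 1 | 4 | 4 | 0 of 5 | 1 of 5 |
| 2 | 3 | 3 | 1 of 5 (20%) | 2 of 5 (40%) |
| 3 | 2 (same day as the 48-hour sample) | 2 | 2 of 5 (40%) | 3 of 5 (60%) |
| 4 | 1 (before the 48-hour sample) | 2 | 2 of 5 | 3 of 5 |
| 5 | 0 (enrolment) | 2 | 2 of 5 | 3 of 5 |
| 6 or more | before enrolment | 2 | 2 of 5 | 3 of 5 |

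**Interval to the next scheduled LFT, k = 3 or more**
- Dosing 0–4: follow-up on day 4 + 14 = 18, and 18 − 2 = 16 days after the 48-hour sample.
- Dosing 1–5: follow-up on day 5 + 14 = 19, and 19 − 2 = 17 days.

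**Which k to expect.** Two texts bear on this. Section 7 screens admitted patients with fever of under 72 hours, which puts them at about illness day 1 to 3 at screening. Enrolment can be later, and the condition is not repeated in the inclusion criteria (5.1). Entry also needs platelets of 30,000/µL or below, and the background says: "Typically platelet counts decline steeply during the infection within the initial 4-6 days of onset of fever". So early entry is possible and entry on day 3 or later is not excluded. The documents do not give the split.

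**If 2.3.1 is followed,** no dosing day lacks an LFT for any k. The mandatory stop still applies to one value only.

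**The case against.** The strongest reply is that 8.2.1 is the outlier. Section 2.3.1 says daily; the Schematic lists routine biochemical assays during treatment, including in the final-dose box; and section 9 has LFTs during the study period. Section 2.3.1 itself mentions routine biochemistry and LFTs together, so it is natural to read the Schematic's assays as including them. Section 7 also refers to a Schedule of Events (Appendix IV), which is not shown and may settle the matter. This stands as a limit: a reader might infer that patients will certainly go untested at the end of dosing, and the documents do not support that. It does not remove the conflict, because the Schematic and section 9 do not give LFT days and 8.2.1 does.

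The illness-day wording may be a slip for study day 5, which the protocol uses elsewhere as the end of daily follow-up. LFTs would then fall on study days 0, 2 and 5, and the end-of-dosing gap would close under either dosing reading. This is plausible but cannot be shown from the text. The correction is the same small edit.

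A reader might also infer that most patients enter on illness day 3 or later. The screening text on fever of under 72 hours prevents that conclusion.

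On the stop, a single mandatory check can be defended: 8.2.1 notes that liver dysfunction may come from dengue itself, a physician sees patients daily until discharge, and 5.5 allows withdrawal. But 5.5 sets no on-treatment ALT threshold and needs a result to act on. Having chosen to stop at 250 U/L despite that caveat, the protocol gives no reason for dropping the rule after 48 hours.

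Nor is the week-2 LFT only a telephone report: patients are asked to attend as well, and the Schematic includes biochemistry at that follow-up.

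**Conclusion.** The conflict between 2.3.1 and 8.2.1 is plain in the current text and should be resolved. The untested period is conditional on 8.2.1 being followed as worded. It is then 2 dosing days for entry on illness day 3 or later, 1 for day 2 and 0 for day 1, each rising by one if dosing runs on study days 1 to 5. How many patients would be affected cannot be stated, and Appendix IV could show that daily testing was intended.

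The narrow ALT stop is a separate weakness that remains under either schedule. It is a design choice and not a contradiction, but it lets the same ALT value stop drug in one patient and not in another, depending on the day it was measured.

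Because ALT above 150 U/L is an exclusion criterion, a reader might also infer that 5.5 must be edited so that a new value above 150 U/L does not lead to withdrawal. The documents do not require this. Such an edit would remove a possible safety ground for withdrawal and is a matter of judgement.

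**What to change.** 1. In 8.2.1, replace the illness-day time point with the last dosing day on the study clock (study day 4 or 5, stated once the dosing days are fixed).
2. Make 2.3.1, 8.2.1 and Appendix IV state one LFT schedule. The preferred one is daily while dosing plus week 2, as 2.3.1 already promises. The minimum is study days 0, 2 and the last dosing day plus week 2, with 2.3.1 amended to match. Either leaves no dosing day after the last on-treatment LFT, whatever the illness day at entry.
3. Extend the stop, for example: *Study drug is stopped if any on-treatment ALT from the 48-hour sample onward exceeds 250 U/L.*
4. Leave 5.5 as it is.

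The cost is amendment wording and a check of Appendix IV. The minimum schedule keeps four time points and moves one; the daily schedule adds nothing beyond what 2.3.1 promises. The downside is a few more drug stops for ALT rises caused by dengue itself.

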1. ASSESSMENT OF SAFETY

All data on potential adverse events, if any, will be recorded in a questionnaire/checklist. Further safety assessment will be also be done by monitoring for vital signs, laboratory evaluations – CBC – LFTs –Renal Function Tests during the study period with a follow-up at 2 weeks after stopping the medications.

Adverse Event / Experience

Any untoward medical occurrence associated with the use of CPLE (Caripill) in severe thrombocytopenic dengue patients whether or not considered drug related will be recorded on a AE grading scale (– Grade 1 Mild; asymptomatic or mild symptoms; clinical or diagnostic observations only; no intervention indicated – Grade 2 Moderate; minimal, local or noninvasive intervention indicated; limiting age-appropriate instrumental ADL – Grade 3 Severe or medically significant but not immediately life threatening; hospitalization or prolongation of hospitalization indicated; disabling; limiting self care ADL – Grade 4 Life-threatening consequences; urgent intervention indicated. – Grade 5 Death related to AE). All Serious Adverse Events regardless of causality will be reported.

1. STATISTICAL CONSIDERATIONS

**10.1 Sample size**

This is an exploratory study focusing primarily on efficacy of CPLE (Caripill) and based on earlier efficacy studies in mild and moderate dengue, a target sample size of 50 patients in 2 cohorts was chosen for enrolment over one year of dengue season based on clinical judgement and feasibility considerations.

Specifically, this study will have 80% power to detect an increase in platelet count and hematocrit levels by 20% due to CPLE (Caripill) therapy.

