15 APPENDICES LIST …………………………………………………………………………………………………………..……….33

LIST OF ABBREVIATIONS

| AE | Adverse Event/Adverse Experience |
| --- | --- |
| CONSORT | Consolidated Standards of Reporting Trials |
| CRF | Case Report Form |
| CPLE | *Carica papaya* leaf extract |
| GCP | Good Clinical Practice |
| ICF | Informed Consent Form |
| ICH | International Conference on Harmonization |
| IRB | Institutional Review Board |
| LFT | Liver Function Tests |
| AST | Aspartate Aminotransferase |
| ALT | Alanine Aminotransferase |
| MOP | Manual of Procedures |
| N | Number (typically refers to subjects) |
| PI | Principal Investigator |
| SAE | Serious Adverse Event/Serious Adverse Experience |
| SOP | Standard Operating Procedure |
| UP | Unanticipated Problem |
| WHO | World Health Organization |

PROTOCOL SUMMARY

| **Title:** | A prospective study to evaluate the safety and efficacy of *Carica papaya* leaf extract (oral CPLE (Caripill)) in the treatment of severe thrombocytopenia (≤30,000/µl) in dengue |
| --- | --- |
| **Précis:** | This will be a placebo-controlled, single center, randomized prospective study of CPLE (Caripill) (*Carica papaya* leaf extract) tabs in dengue patients with severe thrombocytopenia (platelets ≤ 30,000/ul). The study will enroll 100 eligible dengue cases into the two arms of the study – one arm receiving CPLE (Caripill) 1100mg *t.i.d* for 5 days and the other group receiving placebo. |
| **Objectives:** | Primary: To determine the impact of CPLE (Caripill) administration (1100mg *t.i.d* for 5 days on the following:   - Platelet count and hematocrit values in dengue patients with severe thrombocytopenia. - Reducing the number of blood product transfusions *esp.* platelet transfusion and - All-cause mortality rates. |
|  | Secondary: To evaluate the effect of CPLE (Caripill) administration (1100mg *t.i.d* for 5 days) on the following-   - Magnitude and kinetics of serum viremia (or NS1 antigenemia). - Magnitude and kinetics of cytokines IFNγ, IL6, TNFα and IL4. - The total length of hospital (ICU & ward) stay, |
| **Population:** | Study cohort of 100 adults, either gender (more than 18 yrs old, non-pregnant) and admitted to AIMS Hospital and diagnosed of dengue with moderate to severe thrombocytopenia. |
| **Number of Sites:** | Dept. of General Medicine and Dept. of Emergency Medicine, Amrita Institute of Medical Sciences and Research Center, [name]. |

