**Schematic of Study Design**

For 50 cases: Obtain informed consent. Screen potential subjects by inclusion and exclusion criteria; obtain history and fill in the Clinical Research Form (CRF).

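### The planned size is stated inconsistently (100 patients, 50 cases, or 50 in 2 cohorts), so the 80% power statement and the 30% interim trigger have no clear N

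*Protocol*

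**What the plan says.** Places that give 100 patients, or 50 per arm:

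- Protocol Summary, Précis: "The study will enroll 100 eligible dengue cases into the two arms of the study".
- Protocol Summary, Population: "Study cohort of 100 adults, either gender".
- Section 5, Study Enrollment and Withdrawal: "A total of 100 cases of dengue with a thrombocytopenia". The same section places enrolment at the moment the consent form is signed and dated.
- Schematic of Study Design, arm boxes: "Treatment Group (N=50" and "Control Group (N=50".

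Places that give 50, or can be read that way:

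- Schematic of Study Design, opening box on consent, screening and history: "For 50 cases: Obtain informed consent".
- Section 10.1, Sample size: "a target sample size of 50 patients in 2 cohorts was chosen for enrolment over one year of dengue season". The section bases this number on clinical judgement and feasibility. It then claims 80% power for a 20% increase in platelet count and hematocrit, without naming the N, the SD, the control mean, the significance level or the test.

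Two further passages depend on the number. Section 10.4 sets an interim efficacy look when 30% of patients have been followed. Section 10.2 defines the primary analysis population through a cohort 1, from which it takes the placebo patients, and a cohort 2, from which it takes everyone whatever their assignment.

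**The concern.** Section 10.1 is where a reader looks for the size of the trial, and it never says per arm, each, or 100. The schematic's first box gives 50 for steps that come before randomization, so it is not naturally a per-arm figure. A reader who starts from these two places could take 50 as the total. A reader who starts from the Summary or Section 5 will take 100.

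Three things rest on the number: when enrolment ends, which design the 80% power describes, and when the interim look takes place. A factor of two in N is a factor of the square root of 2, about 1.41, in the standard error of the treatment difference.

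**Working it through.** **1. Do the statements agree?**

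| Place | Figure | Agrees with 100? |
|---|---|---|
| Protocol Summary (twice) | 100 | yes |
| Section 5 | 100 | yes |
| Schematic, arm boxes | 50 + 50 = 100 | yes |
| Schematic, consent and screening box | 50 | no |
| Section 10.1 | 50 in 2 cohorts | yes if 50 in each (2 × 50 = 100); no if 50 in all (25 + 25) |

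The consent box is the firm contradiction. Patients who consent and are screened must be at least as many as those randomized, and 50 is fewer than 50 + 50. Because Section 5 defines enrolment by signature of the consent form, 50 consents would also mean 50 enrolled, against 100 in that section.

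Section 10.1 is ambiguous rather than contradictory. Section 10.2 might have resolved it if cohort meant arm. But its cohort 2 holds patients of differing treatment assignment, and its cohort 1 has placebo patients picked out of it, so the cohorts there are not the two arms.

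**2. Interim trigger.** 0.30 × 100 = 30 patients; 0.30 × 50 = 15 patients.

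**3. Can the 80% be reproduced?** No. The inputs given are a 20% increase, 80% power and 1:1 allocation. SD, control mean, alpha and test are not given. The most that can be done is to work backwards under an assumption, here a two-sided 5% comparison of two means with n per arm:

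- d = (1.960 + 0.842) × √(2/n), where d is the difference in SD units
- power = Φ(d × √(n/2) − 1.960)

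*If the 80% refers to 50 per arm:* d = 2.802 × √(2/50) = 0.560. At 25 per arm, power = Φ(0.560 × √12.5 − 1.960) = Φ(0.021) = 50.8%. With the t distribution, d = 0.566 and power is 50.0%.

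*If the 80% refers to 50 in total (25 per arm):* d = 2.802 × √(2/25) = 0.792, and power at 50 patients is 80% by construction. At 50 per arm, power = Φ(0.792 × √25 − 1.960) = Φ(2.002) = 97.7%. With the t distribution, d = 0.809 and power is 98.0%.

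Other significance levels (normal approximation):

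| Alpha | 80% set at 50 per arm: power at 25 per arm | 80% set at 25 per arm: power at 50 per arm |
|---|---|---|
| 5%, one-sided | 54.5% | 96.9% |
| 5%, two-sided | 50.8% | 97.7% |
| 2.5%, two-sided | 47.6% | 98.3% |
| 1%, two-sided | 43.7% | 98.8% |

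**4. What SD does each reading imply?** Take the 20% as a difference relative to the control mean, with CV the SD divided by that mean. Then CV = 0.20/d: 0.20/0.560 = 0.357 for 50 per arm and 0.20/0.792 = 0.252 for 25 per arm. As the protocol gives no CV, here is a range (two-sided 5%, normal approximation):

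| Assumed CV | Power, 50 per arm | Power, 25 per arm |
|---|---|---|
| 0.25 | 98% | 81% |
| 0.357 | 80% | 51% |
| 0.50 | 52% | 29% |
| 0.60 | 39% | 22% |

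The same sentence about 80% power thus fits two designs that differ twofold in size, and nothing in Section 10.1 says which.

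**The case against.** The strongest reply is that the intended total is not really in doubt. Section 5 states 100 plainly, the Summary says it twice, and the schematic's arm boxes add up to it. Read with these, Section 10.1 most sensibly means 50 in each of two groups. The schematic has been flattened to text, so the position of its first box cannot be seen, and the arm boxes in the same figure rule out 50 as the trial total. Stopping at 50 would mean overriding the explicit enrolment statement.

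Most of this stands. 100 is the better-supported total, and Section 10.1 alone is no contradiction. What remains is that the words of the consent box are intact and cannot be squared with the arms below it, and that Section 10.1 leaves its own N to be inferred.

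A reader might go further and infer that the plan cuts an 80% design to about 50% power. The documents do not support that. If Section 10.1 means 50 per cohort, N is 100 and nothing is lost. If it means 50 in total, the 80% that follows describes 50 patients, and power at 50 is 80% as claimed. The fall occurs only if the 80% belongs to 100 patients and enrolment nevertheless stops at 50. That is the consequence of a misreading, not a property of the plan.

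**Conclusion.** The point holds as an inconsistency in a figure the trial relies on. One statement (the consent and screening box) conflicts with the rest, and one (Section 10.1) is ambiguous by a factor of two. The interim look is consequently at 30 or 15 patients, and the 80% power has no identified N.

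The power figures of about 50%, or 80% and about 98%, are conditional illustrations. They rest on an assumed two-sided 5% comparison of two means and on an assumed link between the 80% and one of the two sizes; across the alpha choices shown, the first ranges from 44% to 55%. They do not show that the trial is underpowered. Nor do they show that 80% is right at 50 per arm, since no SD, alpha or test is given to check it. The correction should be made because the number governs the end of enrolment and the interim timing, and because it costs almost nothing.

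**What to change.** - Section 10.1: write *100 patients in total, 50 per arm*.
- Schematic, first box: change the count from 50 to 100 cases.
- Section 10.4: state the interim look as 30 of 100 patients.
- Section 10.2: replace or correct the cohort 1 and cohort 2 wording, so that the analysis population is described in terms of the two randomized arms, or define the cohorts if they are meant to be something else.
- Section 10.1, power sentence: say which N the 80% refers to and give the SD, alpha and test behind it. If 80% does not hold at 50 per arm, restate the power at that size. Attaching the 80% to 100 patients without these inputs would only repeat an unsupported claim.

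The first four are wording changes and add no patients, because 100 is already the figure in the Summary and Section 5. The last needs the original calculation to be retrieved or a short one done; if no calculation exists, the honest course is to present the size as one of feasibility and report the detectable difference at 50 per arm under a stated range of SDs.
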